##### Follow-up data

The primary outcome will be the ACT scores. The primary analysis will compare the two groups in 3 months. A secondary analysis will compare the two groups at 6,9 months to assess if any differences between groups have been maintained over time.

Loss to follow-up is likely to lead to biased estimates of intervention effect. We will try to avoid bias due to attrition by carefully following up the participants in both groups. We will phone participants who fail to complete questionnaires after a second reminder. We anticipate a 20% loss to follow-up in this trial, and will implement procedures to minimize loss to follow-up and patient withdrawal, and where possible, we will collect information on reasons for patient withdrawal.

#### Data integrity

The integrity of trial data will be monitored by regularly scrutinizing data sheets for omissions and errors. Data will be double entered and the source of any inconsistencies will be explored and resolved.

#### Sample size

We wished to estimate the sample size according to non-inferiority clinical trial between the heat-sensitive and drug group. Sample size depends on the level of confidence chosen, the risk of type II error (or desired power), and δ. The parameter margin of non-inferiority δ can be specified as a difference in means or proportions. It is often chosen as the smallest value that would be a clinically important effect. To determine δ, we carried out a small sample pilot study previously. The primary endpoint chosen was ACT. The result of outcome showed difference in means between the two groups approximately was 0.45. The choice of δ = 0.15 (30% of Δ) appeared to be reasonable based on clinical relevance and statistical judgment.

If we apply a two-sided 5% significance level(δ = 0.15, α = 0.05, β = 0.2), 95% power the calculated required sample size is approximately 120 participants in each group, according to the following equation. Allowing for a 20% loss to follow up, a total of 144 participants will be required in each group, with 288 participants in total.

$$n=2\times \frac{{\left(U_{\alpha }+U_{\beta }\right)}^{2}}{\gamma^{2}}\times P(1-P)$$

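### The sample-size sentence gives both β = 0.2 and 95% power, but β = 0.2 means 80% power

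*Protocol article*

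**What the plan says.** The Sample size section of the protocol article describes a non-inferiority calculation and names among its inputs "the risk of type II error (or desired power), and δ". It sets the other inputs in this way: "If we apply a two-sided 5% significance level(δ = 0.15, α = 0.05". The sentence then continues "β = 0.2), 95% power the calculated required sample size is approximately 120 participants in each group". An allowance for 20% loss to follow-up brings this to 144 per group and 288 in total.

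The equation printed below the text is n = 2 × (U_α + U_β)² / γ² × P(1 − P). The section states no value for P. The symbol γ is not defined, and the natural reading is that it stands for the margin δ. The Statistical analysis plan section repeats the two-sided 5% level but says nothing about power, and no other section gives a power figure.

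**The concern.** The section treats the type II error risk and the desired power as alternative ways of stating one input, so β carries its usual meaning and power is 1 − β. A single calculation has one β. This one is given β = 0.2 in the parenthesis and 95% power immediately after it.

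Power is one of the figures on which the size of the trial is justified. Here it is the probability of demonstrating non-inferiority when the two treatments are truly equivalent. One statement puts the risk of missing that at 5%, the other at 20%. A reader judging whether 288 participants are enough, or how much weight to give a result that fails to show non-inferiority, cannot tell which applies.

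**Working it through.** **Inputs from the Sample size section.** Margin δ = 0.15; α = 0.05, two-sided; β = 0.2; stated power 95%; n = 120 per group; 20% loss; equal groups. P is not stated. I read γ as δ.

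**Step 1: the direct check.** Power = 1 − β = 1 − 0.2 = 0.80. For power 0.95, β = 1 − 0.95 = 0.05. The two printed values conflict whatever P is.

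**Step 2: can 120 be reproduced?** Only by solving for the missing P. Rearranging the printed equation:

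P(1 − P) = n δ² / [2 (U_α + U_β)²], with n δ² = 120 × 0.0225 = 2.70.

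| Level | Power | U_α + U_β | P(1 − P) for n = 120 | P |
|---|---|---|---|---|
| two-sided 5% | 80% | 1.960 + 0.842 = 2.802 | 0.172 | 0.78 or 0.22 |
| two-sided 5% | 95% | 1.960 + 1.645 = 3.605 | 0.104 | 0.88 or 0.12 |
| one-sided 5% | 80% | 1.645 + 0.842 = 2.487 | 0.218 | 0.68 or 0.32 |
| one-sided 5% | 95% | 1.645 + 1.645 = 3.290 | 0.125 | 0.85 or 0.15 |

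The article states the two-sided level; the one-sided rows are there for sensitivity. Each row gives an admissible P, so the figure of 120 does not reveal which power produced it.

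**Step 3: what the difference is worth.** At fixed P and δ, the required n is proportional to (U_α + U_β)². For the two-sided level the ratio is (3.605 / 2.802)² = 1.66.

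- If 120 gives 80% power, 95% power needs 120 × 1.656 = 198.7, about 199 per group (one-sided: about 210).
- If 120 gives 95% power, 80% power needs 120 / 1.656 = 72.5, about 73 per group (one-sided: about 69).

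With the article's own multiplication by 1.2 for losses, 199 becomes 239 per group (478 in total) and 73 becomes 88 per group (176 in total), against the planned 288.

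**Step 4: range over P.** P is unknown, so the values below are assumptions (two-sided 5%, δ = 0.15).

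| Assumed P | n per group, 80% power | n per group, 95% power | Power with 120 per group |
|---|---|---|---|
| 0.5 | 175 | 289 | 64% |
| 0.7 | 147 | 243 | 72% |
| 0.8 | 112 | 185 | 83% |
| 0.9 | 63 | 104 | 97% |

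Depending on P, 120 per group could give power well below 80% or slightly above 95%.

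**Step 5: the remaining figures.** 120 × 1.2 = 144 and 2 × 144 = 288, as stated. They follow from 120 and carry no information about the power.

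**The case against.** The strongest reply is that this is a slip of wording. The parenthesis lists the values that enter the equation, and β is one of them; the 95% appears only in the running text. The section also names the confidence level as an input, so 95% may have been meant as the confidence level matching the 5% significance level. On that reading 120 and 288 stand, 80% is a conventional power, and one phrase changes.

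That is plausible but cannot be shown from the article. The text says power, and the 5% level is already given separately. If it is a slip, the correction is still needed, because the declared power drops to 80%.

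Other limits do stand. The figure of 199 per group applies only if 120 was computed with β = 0.2 and 95% was intended; if 120 was computed at 95%, the trial is not underpowered against its stated aim. The solved values of P rest on the two-sided level and on reading γ as δ, and they are not needed to prove the contradiction. A failed non-inferiority result would in any case be judged from the observed interval against the margin, so the planned power affects its interpretation only indirectly. An article may leave the value of P to the full protocol, so its absence alone is not the fault; it matters here because it removes the only means of telling which power was used.

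**Conclusion.** The contradiction holds on the face of the sentence and needs no assumption: β = 0.2 is 80% power, not 95%. The two statements put the type II error at 20% and 5%, and they correspond to sample sizes that differ by a factor of 1.66 under the article's own equation with a two-sided 5% level (1.75 if one-sided). The sizes in either direction, about 199 or about 73 per group, are conditional on which value produced 120, and the article does not settle that. It is not shown that 120 per group is wrong. It is shown that the power claimed for it is contradicted and cannot be recovered from the text. Because power is a core design figure, the sentence should not stand as written.

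**What to change.** State one matching pair of values, taken from the calculation actually performed:

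- If β = 0.2 was used, replace 95% power with 80% power.
- If 95% power was used, replace β = 0.2 with β = 0.05.

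In either case give the value of P that was entered, define γ, and say whether U_α is one-sided or two-sided, so that 120 can be reproduced. If a formula for means was in fact used, give that formula and its standard deviation instead, since the printed equation has no such term.

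The text change is about one line. The cost is in what it may reveal: if 120 came from β = 0.2, the declared power falls to 80%. If 95% was truly intended, the sponsor must either accept 80% or recruit about 199 evaluable participants per group at the same P and margin.

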### Outcome measures

#### Primary outcome

At present, the goal of asthma care is to achieve and maintain control of clinical manifestation of the disease [27,28]. Hence, we use Asthma Control Test (ACT) to quickly access asthma control, a simple 5-question tool that is completed by the patient and parents/caregivers and recognized by the National Institutes of Health (Table 1)[29,30]. Patients should write the number of each answer in the score box provided, and then add up each score box for your total. ACT will be assessed before treatment and at days 15, 30, 60, and 90 in the treatment period. Follow-up visit will be at 3, 6 months after the last treatment session.

**Table 1 T1:** Asthma Control Test (ACT) for people 12 yrs and older.

1. In the past 4 weeks, how much of the time did your asthma keep you from getting as much done at work, school or at home?					Score
All of the time ①	Most of the time ②	Some of the time ③	A little of the time ④	None of the time ⑤	

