#### Outcome data

For primary and secondary outcome measures, these will be summarized descriptively (mean, SD, median, minimum and maximum) at each time point by treatment group. The t-test, Mann-Whitney U and Wilcoxon test were used for comparison of variables, as appropriate.

All adverse events reported during the study will be included in the case report forms; the incidence of adverse events will be calculated. The percentage of subjects with adverse events in each group will be calculated and compared using the chi-squared test or Fisher's exact test.

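### The sample-size equation uses a proportion's variance, but the endpoint and margin are in mean ACT score, so 120 per group and its power do not apply to the primary analysis

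*Protocol article*

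**What the plan says.** The Sample size section of the protocol article sets the design as non-inferiority: "We wished to estimate the sample size according to non-inferiority clinical trial between the heat-sensitive and drug group". It names the endpoint, "The primary endpoint chosen was ACT", and gives the pilot result: "The result of outcome showed difference in means between the two groups approximately was 0.45". The margin δ = 0.15 is taken as a fraction of that difference. The section then says that "the calculated required sample size is approximately 120 participants in each group, according to the following equation", and the equation is n = 2 × (Uα + Uβ)² / γ² × P(1-P). It gives no value for P and no SD, and γ is not defined. A 20% allowance for loss to follow-up brings the figure to 144 per group and 288 in total.

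Elsewhere ACT is a numeric score. Under Primary outcome, patients answer five items scored 1 to 5 and "then add up each score box for your total". Under Follow-up data: "The primary outcome will be the ACT scores. The primary analysis will compare the two groups in 3 months". Under Outcome data, outcomes are summarised by mean and SD, and "The t-test, Mann-Whitney U and Wilcoxon test were used for comparison of variables, as appropriate". No ACT cut-off or responder rate is defined anywhere in the article.

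**The concern.** P(1-P) is the variance of a yes/no outcome and can never exceed 0.25. For a summed score the variance must come from the SD of that score, which the printed equation does not contain. Using P(1-P) for a mean assumes, without saying so, an SD of at most 0.5 points on a scale 20 points wide.

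The 288 participants rest on this calculation, and the Discussion describes the aim as finding a treatment that matches conventional drug therapy. If the claimed power does not belong to the primary comparison, the trial could end with a confidence interval several times wider than the margin. An inconclusive result could then be misread as showing that the two treatments are alike.

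**Working it through.** **Inputs from the Sample size section:** δ = 0.15 (γ in the equation is read as δ); α = 0.05, two-sided; β = 0.2, so 80% power; n = 120 per group. The same sentence also states 95% power, so both values are tried. **Not given:** P and the SD of ACT. Every SD below is an assumption.

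**1. Trying to reproduce 120.** At a two-sided 5% level and 80% power the multiplier is

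2 × (1.960 + 0.842)² / 0.15² = 697.7

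so n = 697.7 × P(1-P). For n = 120, P(1-P) = 120 / 697.7 = 0.172, which gives P ≈ 0.78 (or 0.22). Other readings of the stated α and power give:

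| Level and power | P needed for n = 120 (or 1 minus this) |
|---|---|
| Two-sided 5%, 80% | 0.78 |
| One-sided 5%, 80% | 0.68 |
| Two-sided 5%, 95% | 0.88 |
| One-sided 5%, 95% | 0.85 |

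The figure of 120 can be reached only by choosing a P that the article does not state.

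**2. What this implies for a mean.** The matching formula for means is n = 2 × (Uα + Uβ)² × SD² / δ², so P(1-P) stands where SD² should be. The implied SD is √0.172 = 0.41 points at 80% power, or 0.32 at 95% power. At P = 0.5 the printed equation reaches its ceiling of 697.7 × 0.25 = 174.4, or 175 per group (289 at 95% power), however variable ACT is.

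**3. The calculation for mean ACT.** With δ = 0.15, two-sided 5% and a true difference of 0:

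- n per group at 80% power = 697.7 × SD²
- standard error at 120 per group = SD × √(2/120) = 0.129 × SD
- power at 120 per group = Φ(0.15 / (0.129 × SD) − 1.96)
- 95% CI half-width = 1.96 × 0.129 × SD
- margin supported at 80% power = 2.802 × 0.129 × SD

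| Assumed SD (ACT points) | n per group for 80% power | Power at 120 per group | 95% CI half-width | Margin that 120 supports at 80% power |
|---|---|---|---|---|
| 0.5 | 175 | 64% | 0.13 | 0.18 |
| 1 | 698 | 21% | 0.25 | 0.36 |
| 2 | 2,791 | 8% | 0.51 | 0.72 |
| 3 | 6,280 | 6% | 0.76 | 1.09 |
| 4 | 11,163 | 5% | 1.01 | 1.45 |

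At SD 2 to 4 the half-width is 3.4 to 6.7 times the margin.

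**4. Sensitivity to the true difference.** The article does not say which treatment the pilot difference of 0.45 favoured. If it favoured moxibustion and held in the trial, power at 120 per group would be Φ((0.15 + 0.45) / (0.129 × SD) − 1.96), that is 64%, 34% or 21% at SD 2, 3 or 4. If it favoured the drug, moxibustion would be worse by more than the margin, and the chance of concluding non-inferiority would be below 2.5%, as it should be.

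**The case against.** **The inputs may be in a fuller document.** A journal article condenses the protocol, so the absence of P or an SD from it is not itself a fault. This stands, but neither value would repair the calculation: a binomial variance is wrong for a mean score whatever P is, and the printed equation has no place for an SD.

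**The margin may have been meant as a proportion.** The section remarks in general terms that a margin can be set for means or for proportions, and 120 is compatible with 15 percentage points on a responder rate. This is only a possible reading. P is back-solved, and some P would match any n up to about 174. The pilot basis, the endpoint and the planned tests all concern scores.

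**The score may be on another scale.** If δ were standardised, n would be 698. If ACT were averaged over its five items, an SD of 0.41 would equal 5 × 0.41 ≈ 2.1 points on the total, and δ would equal 5 × 0.15 = 0.75 points. Then 120 would not be absurd. But the article tells patients to sum the items and defines no item average, and P(1-P) would still be the wrong variance term.

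**The size of the shortfall is not known.** This stands. It depends on an SD that the article does not give and on the true difference. At SD 0.5, power at 120 per group is 64%, not single figures. Any statement that the trial would very probably fail must be tied to an assumed SD of about 2 or more and a true difference near zero.

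**Conclusion.** The concern holds. Endpoint, pilot difference, margin and planned tests all refer to ACT scores, while the equation is for a proportion. The figure of 120 per group and the power attached to it are therefore not properties of the primary comparison, and this does not depend on any assumed SD.

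The size does. For 120 to be right for mean ACT at 80% power, the SD would have to be about 0.41 points on the 5 to 25 total. At an assumed SD of 2 to 4 and a true difference of 0, power for a 0.15-point margin is 5% to 8%, and about 2,790 to 11,160 per group would be needed. Even at SD 1, power is 21%. This must be corrected before the sample size is relied on.

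**What to change.** Make endpoint, margin, formula and analysis agree, by one of two routes.

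- **Mean ACT stays primary.** Use n = 2 × (Uα + Uβ)² × SD² / δ². State the SD and its source, and give δ in ACT points with a clinical justification. Report the power or the 95% CI half-width that the planned size delivers, and judge non-inferiority by comparing the 95% CI with δ. If the scale is an item average, say so and score it that way throughout.
- **A responder proportion was intended.** Define the ACT-based response, state the assumed P, express the margin as 15 percentage points, and make the risk difference with its 95% CI the primary analysis.

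Either way, replace the present power claim and settle on a single power value, because β = 0.2 and 95% power cannot both hold. Fix the choice before any unblinded outcome data are seen.

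**Cost.** The first route needs a rewritten sample-size paragraph and an SD. The pilot used ACT, so its data should supply one, though the article does not report it. No extra patients are needed if the planned size is kept and its true precision is stated, but the power or the margin will then look less favourable. Keeping a 0.15-point margin at 80% power would need far more patients at any SD of 1 or above. A wider margin must be justified clinically, not chosen because 120 per group can support it. The second route changes the primary endpoint and analysis, so it needs a formal amendment.

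### The 20% loss allowance is multiplied on (120 × 1.2 = 144) rather than divided out (120/0.8 = 150), so 288 participants cover a loss of at most 16.7%

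*Protocol article*

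**What the plan says.** The Sample size section of the protocol article reports that "the calculated required sample size is approximately 120 participants in each group". For attrition it then says: "Allowing for a 20% loss to follow up, a total of 144 participants will be required in each group, with 288 participants in total".

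Under Follow-up data the article gives the same rate as its expectation: "We anticipate a 20% loss to follow-up in this trial". So 20% is both the allowance built into the sample size and the loss the investigators expect. No other definition of the allowance is given.

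Three other statements bear on the consequence:

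- The Statistical analysis plan section describes an intention-to-treat analysis of randomised participants who have at least one outcome report.
- Dropped or missing data specifies last observation carried forward (LOCF).
- Follow-up data places the primary comparison of the Asthma Control Test (ACT) at 3 months.

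**The concern.** An allowance for loss should make the number left after the loss equal the number required. Because loss is counted among those randomised, the required number has to be divided by the retained fraction. Adding 20% of the required number gives too few.

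At stake is whether the planned 288 meets the article's own requirement at its own expected loss rate. A reader would take 144 per group to mean that 120 per group remain after a 20% loss. They do not.

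**Working it through.** **Inputs, all from the protocol article**

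- Required per group before loss: 120, given as approximate (Sample size).
- Loss: 20% (Sample size, and again in Follow-up data).
- Planned size: 144 per group, 288 in total, equal groups (Sample size).
- Error rates: "δ = 0.15, α = 0.05, β = 0.2", two-sided, with 95% power stated in the same sentence (Sample size).

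**Reproducing the planned figure**

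120 × (1 + 0.20) = 144 per group; 2 × 144 = 288. This matches exactly.

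**The inflation that retains 120**

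n/(1 − loss) = 120/0.80 = 150 per group; 2 × 150 = 300. The plan is 6 per group, or 12 in total, below this.

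**What the planned size delivers**

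- Complete follow-up at 20% loss: 144 × 0.80 = 115.2 per group (288 × 0.80 = 230.4 in total), which is 4.8 per group below 120.
- Largest loss that still leaves 120: 1 − 120/144 = 16.7%.

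**Effect on power, if 120 delivers the power claimed for it**

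In the normal approximation the sum of the two normal quantiles scales with √n, so

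power = Φ[(z_α + z_β) × √(115.2/120) − z_α], with √(115.2/120) = √0.96 = 0.980.

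| Power assumed at 120 | Two-sided 5%: z_α + z_β | Power at 115.2 |
|---|---|---|
| 80% (β = 0.2) | 1.960 + 0.842 = 2.802 | Φ(2.802 × 0.980 − 1.960) = 78.4% |
| 95% | 1.960 + 1.645 = 3.605 | Φ(3.605 × 0.980 − 1.960) = 94.2% |

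The loss is 1.6 or 0.8 percentage points. With a one-sided 5% level the results are 78.6% and 94.3%, so sidedness hardly matters.

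**What cannot be checked**

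The printed formula is for proportions and needs a value of P, which is not stated. The base of 120 therefore cannot be reproduced and is taken as given here.

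**The case against.** The strongest reply concerns the consequence, not the arithmetic.

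1. **The analysis set is wider than those with complete follow-up.** One outcome report is enough for inclusion, and missing values are carried forward. ACT is measured before treatment and at days 15, 30, 60 and 90, so someone lost after day 15 still enters the 3-month comparison. This stands: 115 is the expected number with complete follow-up, and the number analysed may be higher. But a carried-forward value does not restore the information in an observed 3-month score. The plan's own allowance also treats lost participants as not counting towards the 120.

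2. **The 20% has no time point.** Follow-up runs to six months after treatment, while the primary comparison is at 3 months. If 20% is the cumulative loss by the last visit, loss at 3 months could be under 16.7%, and 144 would then suffice. This stands as a possibility, but the article does not split the loss by time. The Sample size section uses 20% as its allowance, so the step should be right for 20%.

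3. **The base is only approximate.** An unrounded base of 115.2 would give 115.2/0.8 = 144. But the article states 120, and 120 × 1.2 fits exactly. If the base really was about 115, then 120 is the figure to correct.

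4. **The effect is minor.** Agreed.

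A reader might infer that the trial fails to deliver its stated power, or that only 115 per group can be analysed. The article supports neither. It states no single power (β = 0.2 means 80%, yet 95% is also written), does not show that 120 achieves either value, and has analysis rules that retain many of those lost.

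**Conclusion.** The inflation step is wrong on the article's own figures. For a requirement of 120 and a loss of 20%, the number to randomise is 150 per group, not 144. The planned 288 tolerates 16.7% loss; at the anticipated 20% it leaves about 115 per group with complete follow-up.

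The error is small: about 5 per group with complete follow-up, 12 randomised in total, and roughly 1 to 2 points of power. The power figures assume that 120 is valid for 80% or for 95%, and that all of the 20% is lost by the 3-month comparison and adds no information.

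Correcting this step alone would not make the sample size sound. The conflict between β = 0.2 and 95% power, and a proportions formula applied to an outcome described by a difference in means, are separate and larger problems with the base.

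**What to change.** Keep 288 and replace the sentence on loss with one of two statements:

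- 144 per group allows for a loss of up to 16.7% while retaining 120; or
- a 20% loss leaves about 115 per group with complete follow-up, with slightly lower power than at 120.

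Either is a one-line change with no extra recruitment. The only cost is a slightly less favourable statement. It would also help to say whether the 20% refers to the 3-month comparison or to the end of follow-up.

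If the base sample size is recalculated, use n/(1 − loss) for the allowance. With 120 and 20% this gives 150 per group, 300 in total, which is 12 more participants than planned. Enrolling to that figure makes sense only once the base of 120 and its power have been settled, since the inflation would then have to be recomputed anyway.
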